### Statistical analysis plan

Baseline characteristics of participants, outcome measures at baseline (liver fat content, blood biomarkers and gut microbial composition) at each period time point will be summarised by diet group using descriptive statistics. The differences between the two interventions (LGI and HGI diet) will be tested by matched-pair Student’s t-test. Two-way repeated measures ANOVA test will be used to evaluate the effects of diets and time sequences on liver fat content, as well as on gut microbial composition and blood biomarkers and/or interactions with liver fat content, gut microbial composition and blood biomarkers. Data will be presented as mean±SD and the significance of difference will be set at p<0.05. Any changes in the planned statistical methods will be documented in the trial report. Data input, cleaning and analysis will be conducted using Stata software package. All analyses will be conducted on University of Nottingham computers/laptops that are regularly backed up to University of Nottingham servers.

Microbiome analyses: OTUs with a relative abundance of <0.1% in every sample will be removed, and relative OTU abundances will be inverse normal transformed before further analysis. Associations between response to LGI diet and OTU abundance at genus level will be predicted using a general linear model adjusted for age, gender and BMI. OTUs will be assumed to be significantly associated with response to the dietary intervention with a value <0.05 after adjusting for false discovery rate.

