## Methods and analysis

### Trial design

This is a randomised 2×2 cross-over mechanistic trial including two arms, each of 2 weeks duration comparing an LGI diet and a control HGI diet based on that defined by Bawden *et al*
21 and Morgan *et al*.^41^ The study design is illustrated in figure 1.

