Soft cheese	51	129	1.5	2.7	12.4	0	34	0.51
Meal total		745	99	23.2	28.4	12.5	35.32	34.96
Dinner								
Lasagne (ready meal)	290	413	42	21.5	17.7	4.9	36	15.12
Apple	174	92	20	1	0.87	2.1	38	7.6
Semi-skimmed milk	150	71	6.8	5.3	2.6	0	25	1.7
Fruit and nuts mix	60	267	24.6	8.4	15	3.9	15	3.69
Meal total		843	93	36.2	36.1	10.9	30.22	28.11
Menu total		1999 kcal	264 g (52.7%)	78 g (15.5%)	71 g (31.8%)	46 g	36.64	94.594

GI, Glycaemic Index; GL, glycaemic load; HGI, High Glycaemic Index; LGI, Low Glycaemic Index.

The GI values of commercial food items are generated from that reported by Henry *et al*,^47^ as well as Nutritics software databases (Nutritics). The dietary GI of the menu is calculated from GI proportional contribution to total carbohydrate using the equation: GI=∑(C_food_/C_total_) × GI_food_; where C_food_ is the amount of carbohydrate contained in each digested food (g), C_total_ is the total carbohydrate in the meal and is the reported GI of the food.^21^ The GL of the diet is calculated based on the dietary GI and the amount of carbohydrate provided (the same in both diets) using the following equation: GL=(GI_food_ × C_food_)/100; where GI is the GI of each digested food and food is the amount of carbohydrate in the food.^21^ Food composition analysis and evaluation were performed using Nutritics software (Nutritics, Dublin, Ireland, 2018).

Participants will be provided with the food at the start of each 2-week diet period and will be clearly instructed on safe food storage and reheating. They will be required to complete dietary compliance sheet on a daily basis. Instructions on dietary compliance will be given at each study period and the dietary compliance records will be reviewed regularly during the intervention to assess their compliance. For the first 1 week prior to the intervention (1-week standardisation), and during the 4-week wash-out period, participants will be asked to avoid eating probiotics, yoghurt and cultured milk drink; if any, to standardise their gut microbiota and avoid any carry-over effects as shown in previous studies.^48 49^ Meal-timing will be standardised among all participants as much as possible during the intervention as well as during the standardisation period.

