### Sample size calculation and justification

The sample size is calculated using nQuery based on previous completed study by Bawden *et al*.^21^ Based on their pilot data, baseline liver fat fractions of both diet groups were 2.4±1%–1.2%, and after 1 week were HGI (High GI)=4.7% ± 2% and LGI=1.6 ± 0.7%. Using a two-group t-test (cross-over analysis of variance (ANOVA)) between the post-diet values with a 0.05 two-sided significance level, this produces a sample size of n=8 in each diet sequence (a total sample size of 16). This sample size has an 80% power to detect a difference in means of 3.1 (the difference between a Treatment 1, µ_1_, of 4.7 and a Treatment 2, µ_2_, of 1.6) with the assumption that the crossover ANOVA sqrt (MSE) is 2.828 (the SD of differences, σ, is 4). Assuming that 40% of people would drop out from cross-over study design, it is expected that at least 24 participants would need to be recruited.

The effect from the pilot study by Bawden *et al* pilot study (n=7) was an average 1.6%±0.7% decrease in liver fat fraction after following a 1-week LGI diet (p<0.05). Given that baseline liver fat fraction was 2.4%, in order to see such change with 80% power (p<0.05) we have doubled the participant numbers to n=16 using nQuery software to detect statistically significant differences.^21^ Our group has recently completed a study (ClinicalTrials.gov Identifier: NCT03844165) in which 84 participants with NAFLD followed either an LGI food enriched diet or their normal diet. Patients who changed their diet were found to have a significant decrease in liver fat after 16 weeks (from 20.4% to 18.8%) and had a statistically significant decrease in fasting glucose levels after the diet compared with the control group patients following their normal diet. This provides strong support to our hypothesis and demonstrates that a simple dietary change can have measurable impact on NAFLD symptoms in a short period. In another previous randomised crossover trial, metabolic changes were seen within 2 weeks in a dietary intervention with 10 participants.^66^ Based on these different approaches, we conclude that a sample size of 16 at the end of the study is sufficient. Assuming a 33% drop-out rate we estimate that it will be necessary to enrol n=24 NAFLD participants to achieve n=16 completing the two diet-interventions. This dropout rate has been reported in other dietary interventional studies.^67^

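### The liver-fat comparison is sized with a crossover ANOVA but tested by a paired t-test without a period term, next to an unranked repeated measures ANOVA whose time factor is undefined

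*Protocol article*

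**What the plan says.** **Sizing.** Under Sample size calculation and justification, the trial is sized as follows: "Using a two-group t-test (cross-over analysis of variance (ANOVA)) between the post-diet values". The inputs are a difference of 3.1 points (4.7 against 1.6), a crossover ANOVA root mean square error of 2.828, an SD of differences of 4, and 80% power at two-sided 0.05. The result is 8 per sequence, 16 in total.

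**Testing.** The Statistical analysis plan section states: "The differences between the two interventions (LGI and HGI diet) will be tested by matched-pair" Student's t-test. It continues: "Two-way repeated measures ANOVA test will be used to evaluate the effects of diets and time sequences on liver fat content". The same ANOVA is also to cover gut microbial composition and blood biomarkers. The section does not say which test is primary for liver fat, what the time-sequence factor is, or whether the t-test compares post-diet values or changes.

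**Microbiome.** The same section adds: "Associations between response to LGI diet and OTU abundance at genus level will be predicted using a general linear model". The covariates are BMI, age and gender, and the false discovery rate is controlled. The model names no HGI, period or participant term. The first secondary objective is LGI versus HGI on the microbiota and the correlation with liver outcomes.

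**The concern.** A crossover ANOVA removes the mean difference between period 1 and period 2 from the error. A paired t-test does not: half the participants have the period difference added to their LGI-HGI difference and half have it subtracted, so it inflates the SD of the differences. The stated 80% power therefore belongs to an analysis that is not clearly the one planned.

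The second test does not settle this, because its meaning depends on the undefined factor. Two unranked tests for one primary comparison in 16 people can also fall on opposite sides of p=0.05, with no rule to say which one counts.

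In the microbiome analysis, a model of the response to one diet alone cannot tell a diet effect from change over time, although the same people also supply a randomised HGI period.

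**Working it through.** **Inputs from the protocol article.** Difference 3.1; SD of differences 4 (check: 2.828 × √2 = 4.00); 8 per sequence, N = 16; two-sided alpha 0.05. **Assumed.** The period effect π (period 2 minus period 1, in points of liver fat) is not given, so it is varied from 0 to 4.

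**1. Reproduce the stated size.** For the crossover ANOVA the noncentrality is 3.1/(4/√N) with N − 2 df.
- 7 per sequence (N = 14, 12 df): power 75.9%.
- 8 per sequence (N = 16, 14 df): noncentrality 3.1/(4/4) = 3.1, power 82.2%.

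Eight is the smallest number per sequence that reaches 80%, so the plan's figure reproduces. A parallel-group t-test with SD 2.828 and 8 per group would give only 53%, so the crossover reading is the intended one.

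**2. Paired test without period.** With 8 + 8 completers the period effect cancels from the mean difference but stays in its variance. The expected squared SD of the differences is (15 × 16 + 16π²)/15. For π = 2 this is (240 + 64)/15 = 20.27, an SD of 4.50. The 95% CI half-width is then about 2.131 × 4.50/4 = 2.40. The period-adjusted half-width is 2.145 × 4/4 = 2.14 for every π.

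| Assumed π (points) | Paired t, 15 df: power | Paired t: type I error | Paired t: CI half-width | Period-adjusted, 14 df: power |
|---|---|---|---|---|
| 0 | 82.6% | 5.0% | 2.13 | 82.2% |
| 1 | 81% | 4.3–4.4% | 2.20 | 82.2% |
| 1.6 | 78% | 3.6% | 2.31 | 82.2% |
| 2 | 75% | 2.9–3.0% | 2.40 | 82.2% |
| 3 | 66% | 1.5% | 2.70 | 82.2% |
| 4 | 53% | 0.6% | 3.06 | 82.2% |

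Paired-test power and type I error come from simulation and from numerical integration over the noncentral chi-square distribution of the error sum of squares (noncentrality 16π²/4² = π²). Where both were run they agree to rounding.

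**3. What the repeated measures ANOVA could be.**
- If the time factor means period, a model with participant, diet and period is the crossover ANOVA used for sizing: 32 post-diet values − 1 − 15 − 1 − 1 = 14 error df.
- If it means sequence, it is a between-person factor and cannot be a repeated one.
- If it means before and after each diet, the layout is a complete two-way one, but it has no period term. Its diet-by-time interaction is then a paired test on change scores, and its diet main effect averages pre-diet and post-diet values. Neither is the post-diet contrast that sized the trial.

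The text does not choose among these.

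**4. Genus-level model.** The objective compares two diets; the model names one. If response means change over the LGI period, it contains the LGI effect plus any change over time, and no term in the model separates the two.

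**The case against.** **Period may already be in the plan.** A reader might infer that every planned test omits period. The documents do not support that: under one reading the repeated measures ANOVA is exactly the crossover model. What stands is that the factor is undefined and the tests are unranked.

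**The loss may be small.** It exists only if there is a period effect. With none, the paired test is marginally the more powerful. The one NAFLD change that the article reports is 1.6 points (20.4% to 18.8%) over 16 weeks of an active diet; a period effect of that size leaves 78% power. Effects of 3 to 4 points are about as large as the target difference or larger. The error is conservative, so it creates no false positives. All of this stands.

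**A period effect is not shown to be likely.** It is tempting to argue it from the unequal run-in, "For the first 1 week prior to the intervention (1-week standardisation), and during the 4-week wash-out period", or from entry on high CAP and high habitual GI. But the restriction concerns probiotics, yoghurt and cultured milk drinks and is aimed at the gut microbiota. Regression to the mean after screening would fall mainly before either post-diet scan. Neither is good evidence of a period difference in liver fat.

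**Bias.** A reader might infer bias from unequal completers. Participants and recruitment provides for replacement in the same diet group and recruitment until 16 complete. With 8 + 8, omitting period does not bias the diet estimate.

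**Microbiome.** The diet effect on microbial composition is assigned to the repeated measures ANOVA, so HGI is not dropped from the microbiome analysis as a whole. The sizing concerned liver fat only, so the genus model cannot be faulted for not matching it. Response is undefined and could be meant relative to HGI. The weakness of the model as written, with no control period named, remains.

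**Pre-diet values.** Their role as covariates is detail that a separate analysis plan may hold, and any precision gain would rest on correlations that the article does not give.

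**Conclusion.** The concern holds in a limited form. The test named for the diet comparison is not the analysis that sized the trial. The second test cannot be identified from the text, and no rule says which one decides.

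The cost in power is nil with no period effect, about 1 to 2 percentage points at a 1-point period effect, about 7 at 2 points and about 16 at 3 points. These figures rest on the plan's own difference of 3.1 and SD of 4, on 8 completers per sequence, and on period effects that are assumed. The primary estimate stays unbiased and its type I error does not rise. This is therefore a worthwhile clarification and a cheap safeguard for the stated power, not a defect that invalidates the comparison.

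The genus-level point is secondary: its fault is the missing control period, not mainly a loss of precision.

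**What to change.** 1. Name a single primary analysis: the crossover model for post-diet MRS liver fat with diet, period and participant, with sequence as a between-person term. Its LGI-HGI contrast decides the primary objective.
2. Define the time-sequence factor, or replace the repeated measures ANOVA by the model in item 1.
3. Keep the matched-pair t-test as a sensitivity analysis and say that it compares post-diet values.
4. Fit the genus-level model to both diet periods, with diet, period and participant terms, or use within-person LGI-HGI differences. Define response, and keep the false discovery rate control.

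**Cost.** One error degree of freedom for the primary test (14 in place of 15), or 82.6% to 82.2% power if there is no period effect. Otherwise it takes only analysis wording and Stata code, with no new data or visits. Record the choice before the allocation is unblinded, since choosing between unranked tests afterwards cannot be repaired.

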All biochemical parameters concentrations will be assessed by a central laboratory that uses standard methods. Standard operating procedures will be followed for all laboratory assays to ensure the high quality and reliability of our generated data. Routine blood tests will be analysed by the accredited laboratories. Samples will be stored in −80 °C freezers until the study ends, under yearly service contract and monitoring systems. Analyses will be done according to assay manufacturer advice and completed by technicians and research staff who are formally trained or outsourced to collaborators or external suppliers where necessary. The insulin resistance will be estimated using homeostatic model assessment of insulin resistance (HOMA-IR). HOMA-IR is calculated according to the equation (HOMA-IR = (FPI×FPG)/22.5); where FPI is fasting plasma insulin, and FPG is fasting plasma glucose.^4^

Gut Microbiota Composition: Each participant will be asked to collect fresh stool sample in a standard laboratory container and bring it to the research centre with an ice pack for storage at −80°C. Stool samples will be processed using a standard commercial kit for (DNA)extraction.^63^ Then, the gut microbiota composition will be assessed using 16S sequencing of rRNA. DNA will be diluted to 20 ng/µL for 16S rRNA amplification and sequencing. Water negative controls will be included from extraction, through PCR to sequencing and select samples were sequenced in duplicate for quality control. The V4 region of the 16S rRNA gene will be amplified using universal primers 355F (CCAGACTCCTACGGGAGGCAGC) and 806R (GGACTACHVGGGTWTCTAAT). Amplified DNA will be sequenced on the MiSeq platform (Illumina). Read filtering and clustering will carried out using the MYcrobiota pipeline. Briefly, chimeric sequences will be filtered using the VSEARCH algorithm within Mothur, and reads will be clustered into operational taxonomic units (OTUs) using closed-reference clustering against the SILVA database v132 based on a 97% similarity. Diversity metrics (Shannon index, observed OTUs and Unweighted UniFrac) will be calculated by rarefying the OTU table down to 7000 sequences per sample 50 times and taking the average. These analyses will be carried out in QIIME V.2 (V.2018.11).^64 65^

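### The microbiome filter sets no minimum number of carriers, so genera carried by one or a few of the 16 participants can enter the response-association tests; a one-sentence prevalence condition would be a cheap improvement

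*Protocol article*

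**What the plan says.** The microbiome paragraph of the Statistical analysis plan section (protocol article) fixes a chain of steps:

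- Filter: "OTUs with a relative abundance of <0.1% in every sample will be removed".
- Transformation: "relative OTU abundances will be inverse normal transformed before further analysis". The response is not said to be transformed.
- Target of the test: "Associations between response to LGI diet and OTU abundance at genus level".
- Model: "using a general linear model adjusted for age, gender and BMI".
- Decision rule: taxa count as associated "with a value <0.05 after adjusting for false discovery rate".

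The paragraph does not state a minimum number of carriers, how ties are ranked, which FDR procedure is used, how response is defined, or which visit's abundances enter the model.

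**The concern.** The filter concerns abundance, not prevalence: a taxon is dropped only if no sample reaches 0.1%. With 16 participants, a genus found in one person tells the model nothing except who that person is. If that person also has an unusual response, every genus private to them looks associated, and all by the same amount. The FDR step treats these as separate supporting results and relaxes its threshold accordingly.

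The microbiota objective, including its correlation with liver outcomes, is the first secondary objective, and the Discussion looks to specific gut microbiota as a basis for monitoring NAFLD. A list of several FDR-significant genera that all come from one participant would look like a consistent signal when it is a single observation.

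**Working it through.** **Inputs**

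- Participants: the Sample size section concludes that "a sample size of 16 at the end of the study is sufficient". That figure reproduces from its stated inputs: noncentrality = 3.1 / (2.828 × √2 / √16) = 3.1, and power = 0.822 on 14 df. With 14 participants power is 0.759, so 8 per sequence is the smallest size reaching 80%. The microbiome model has no stated power or error-rate figure to reproduce.
- Samples: four visits (Abstract), so up to 16 × 4 = 64 stool samples face the filter.
- Residual df: 16 − 5 = 11 (intercept, age, gender, BMI, taxon), assuming one row per participant.
- FDR procedure: Benjamini–Hochberg at 0.05 (assumption).

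**Step 1: the filter.** One of 64 samples at or above 0.1% is enough to keep a taxon.

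**Step 2: the transform.** Take a taxon present in one of 16 people, with average ranks for the 15 tied zeros and Blom scores Φ⁻¹((rank − 0.375)/16.25):

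- carrier, rank 16: Φ⁻¹(15.625/16.25) = 1.769
- the other 15, average rank 8: Φ⁻¹(7.625/16.25) = −0.077

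The two values are the same whether the carrier has 0.1% or 20%. The variable is a rescaled indicator for one person, so the adjusted test is an outlier test on that person's response. The t statistic is the same whichever variable is the outcome, so the direction of the model does not matter.

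**Step 3: the FDR step.** If k taxa share one p-value among m tests, they pass together at p ≤ 0.05k/m. With m = 100:

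| k | p ≤ | \|t\| on 11 df ≥ |
|---|---|---|
| 1 | 0.0005 | 4.86 |
| 3 | 0.0015 | 4.19 |
| 5 | 0.0025 | 3.89 |

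**Step 4: null simulation.** 100 null taxa, of which 20% or 50% have a single carrier (assumption); average-rank ties; 2,000 runs per setting. Monte Carlo standard error at 5% is √(0.05 × 0.95 / 2000) ≈ 0.5 points. Cells give the chance of any false taxon / of three or more; the columns marked ≥4 give the chance of any with at least 4 of 16 carriers required.

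| Response | 20% single-carrier | ≥4 | 50% single-carrier | ≥4 |
|---|---|---|---|---|
| Normal | 5.3% / 0.5% | 4.7% | 4.8% / 2.1% | 5.7% |
| t, 3 df | 13.3% / 2.6% | 5.3% | 19.1% / 12.4% | 5.9% |
| One response shifted 4 SD | 22.1% / 5.8% | 3.2% | 33.7% / 25.4% | 4.0% |
| One response shifted 6 SD | 50.9% / 11.7% | 3.6% | 76.8% / 51.7% | 3.1% |

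With random tie-breaking, the 50%, 6 SD setting falls to 3.5% / 0.05%.

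**Step 5: skewed responses and fewer private genera.** The single-carrier count is varied to allow for merging to genus level (average-rank ties; 95–100 null taxa in the first two rows, 160 in the third; 1,500 runs each). Chance of any false taxon:

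| Single-carrier genera in total | Response proportional to baseline fat | Lognormal response |
|---|---|---|
| 5–10 | 6.6–8.1% | 13–15% |
| 20 | 10.9% | 19.4% |
| 80 | 12.1% | 28.6% |

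With a carrier minimum the rate is 2.7–4.5% throughout. A second set (60 common, 15 two-to-three-carrier and 4–80 single-carrier taxa) gave 9–20% and 14–33%, against 3–6% with a carrier minimum.

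**Is skew plausible?** Box 1 sets a lower limit on liver fat but no upper one. The Sample size section cites a NAFLD cohort averaging 20.4%, and pilot data in which the SD was larger where the mean was larger (4.7 ± 2 against 1.6 ± 0.7). If response means a percentage-point change in liver fat, a long tail is plausible, but that definition is an assumption.

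**The case against.** The case against is substantial, and most of it limits the size of the problem.

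- A reader might infer that the stated FDR control fails. The documents do not support that. With normal responses the error rate is near 5% with or without a carrier rule. If response were a responder/non-responder split with 5–8 responders among 16, a run without a carrier rule gave 1.5–4%.
- A reader might infer that the rank transform cannot help. That holds for average ranks. Random tie-breaking removes the effect, though the results would then depend on a random seed.
- Testing is at genus level, so OTUs seen in one person may merge into genera shared by many. The documents do not show how many single-carrier genera would remain.
- Being below 0.1% elsewhere is not the same as being absent, so the one-person indicator is a limiting case. A taxon kept because of one sample may also be missing from the visit analysed.
- It is tempting to read the filter as 7 reads in one sample (0.1% × 7000). The step of "rarefying the OTU table down to 7000 sequences per sample" is stated only for the diversity metrics, so that figure should not be relied on.
- A reader might infer that the whole microbiota objective is compromised. The low-GI versus high-GI comparison is assigned to the paired t-test and repeated-measures ANOVA; only the response-association model is exposed. The article also says that its small-sample findings need replication.
- A condensed article may leave a prevalence cut-off to a fuller plan. That is fair for tie handling and influence checks. The filter, though, is spelled out as a rule, and as worded it admits single-carrier taxa.

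**Conclusion.** The point holds as a cheap improvement to a stated rule, not as a demonstrated failure of error control. The filter lets genera carried by one or a few participants into the response-association model. Given average-rank ties and a skewed or outlying response, genera private to one person can become FDR-significant together.

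Under the assumed numbers of rare genera, the chance of any false discovery rises from about 5% to roughly 7–30% for skewed or heavy-tailed responses. The rows with one response shifted by 4 or 6 SD go higher, but they are stress tests and not forecasts. The number of genera, the single-carrier share, the shape of the response and the tie rule are all assumptions, so no single figure can be derived from the documents. The primary liver-fat comparison and the between-diet comparison of microbiota are untouched.

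**What to change.** Add one sentence to the microbiome paragraph: after collapsing to genus and before transformation and FDR adjustment, only genera present in a pre-set minimum number of participants are tested. At least 4 of 16 is one example; the exact cut-off is a choice, to be fixed before the data are seen. The existing 0.1% condition can stay alongside it. Report the number of genera tested, and list rarer genera descriptively.

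The cost is that rare genera get no formal test. With 16 participants little is lost, because a genus with one carrier cannot be separated from that person's other characteristics.

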Evidence from animal and human studies also showed that diet is the most important modifying factor in the development of human gut microbiome.^22–24^ Dietary alterations can rapidly change the human gut microbiota composition in relatively short time periods^25–27^ and in as little as 24 hours.^28–30^ Certain dietary factors which modify gut microbiota have been associated with a number of diseases including obesity^31^ metabolic syndrome,^22 32 33^ type 2 diabetes,^34^ immunological dysfunctions.^35^ Such dysbiosis in diet-induced NAFLD has been shown to stimulate hepatic fat disposition and promote NAFLD progression to non-alcoholic steatohepatitis (NASH).^36 37^ This is suggested to be mediated by modulation of gut permeability, dietary choline metabolism, bile acid metabolism, endogenous ethanol production and immune balance.^36 37^ Gut microbiota modulated by diet can increase the energy extraction from the breakdown of non-absorbable polysaccharides with the production of monosaccharides and short chain fatty acids (SCFAs) which are substrates for hepatic de novo lipogenesis and carbohydrate biosynthesis.^38^ Certain SCFAs have also been implicated in improving glucose and lipid metabolism beneficial to the host.^39^ Therefore, there is a potential to modulate gut microbiota through dietary changes as a means of NAFLD prevention or alleviation.^11 40^

We describe here our study protocol designed to assess the effects of a specific defined GI dietary manipulation^21^ on liver fat content and its effects on gut microbiota composition in participants with NAFLD compared with a higher GI diet as a control diet. The diets will be adjusted to each participant to meet their energy requirements and the macronutrient composition of the diets will be carefully controlled ensuring that differences in GL are due to differences in GI.

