### Secondary objectives

To investigate the effects of LGI versus HGI diet on gut microbiota composition and its correlations with liver outcomes in participants with NAFLD following a 2-week intervention period.To investigate the changes in blood metabolic biomarkers (glycaemic, insulinaemic, liver, lipid, haematological profiles, gut hormones and plasma SCFAs) between LGI and HGI diet groups following a 2-week intervention in participants with NAFLD.To evaluate controlled attenuation parameter (CAP) as a tool to test the efficacy of a dietary intervention by comparing its performance characteristics with that of MR Spectroscopy (MRS) as a gold standard.To validate the European Prospective Investigation of Cancer Food Frequency Questionnaire (EPIC-FFQ) in Nottingham NAFLD patients against food diary.

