### Study protocol

Following the screening phase and standardisation week, each participant will experience two, 2-week intervention phases, with a 4-week washout period between interventions. Before and after each intervention period they will attend the Imaging Centre (Sir Peter Mansfield Imaging Centre) for MRI scan measurements and then will attend the Biomedical Research Centre for FibroScan, and blood and stool samples collection. During each intervention phase each participant will be required to consume all the food that has been provided, fill in dietary compliance sheets and complete Visual Analogue Scales (VAS) relating to subjective appetite ratings.

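### The genus-level microbiome model omits pre-LGI liver fat, so if response means liver fat, a marker of LGI response cannot be told apart from a marker of starting steatosis

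*Protocol article*

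**What the plan says.** Four places in the protocol article bear on this.

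- **Statistical analysis plan, microbiome paragraph.** The covariate list is fixed: "response to LGI diet and OTU abundance at genus level will be predicted using a general linear model adjusted for age, gender and BMI". So is the decision rule: OTUs count as "significantly associated with response to the dietary intervention with a value <0.05 after adjusting for false discovery rate". Elsewhere in that section, baseline liver fat appears only among the quantities to be summarised descriptively. The two-way repeated measures ANOVA covers liver fat, microbial composition and blood biomarkers, but it is a separate analysis.
- **Secondary objectives.** The first concerns "gut microbiota composition and its correlations with liver outcomes in participants with NAFLD following a 2-week intervention period".
- **Study protocol and Data collection.** Scans are scheduled around both diets: "Before and after each intervention period they will attend the Imaging Centre". The hepatic fat fraction is obtained by MRS at those visits, so a pre-LGI value exists for every completer.
- **Introduction.** The protocol itself ties the microbiota to liver fat: "Such dysbiosis in diet-induced NAFLD has been shown to stimulate hepatic fat disposition and promote NAFLD progression".

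The article does not define response to the LGI diet, and it does not say at which visit OTU abundance is taken.

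**The concern.** A covariate left out of a linear model distorts the taxon coefficient only if it is related both to the taxon and to the response. The Introduction gives a reason to expect the first link. The second is plausible if response is a change in liver fat or the post-diet value, because both depend arithmetically on the starting value. Box 1 sets a lower limit for liver fat (CAP above 288 dB/m or PDFF above 5%) and no upper limit, so starting fat is free to differ between participants.

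If both links exist, a taxon with no relation to response beyond starting fat can pass the decision rule. False discovery rate control deals with the number of taxa tested, not with this, because the association without starting fat in the model is genuine. What is at stake is interpretation. The Discussion hopes that specific gut microbiota will inform NAFLD monitoring, and for that use a marker of severity and a marker of dietary response are different findings.

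**Working it through.** **Inputs from the article.** n = 16 completers; covariates age, gender and BMI; significance level 0.05. The microbiome model has no sample size or power figure of its own. The 16 comes from the primary comparison and reproduces: with difference 3.1, SD of differences 4 and N = 16, the noncentrality is 3.1/(4/√16) = 3.1 and two-sided power on 14 df is 0.82. That calculation does not bear on the genus-level model except by setting n.

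**Assumptions (not in the article).** rb is the size of the correlation of starting fat with response, ro the correlation of a taxon with starting fat. The taxon has no link to response other than through starting fat.

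**Degrees of freedom.** Intercept + 3 covariates + taxon = 5 terms, so 16 − 5 = 11. Adding starting fat gives 16 − 6 = 10.

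**Induced correlation.** With starting fat left out and the covariates unrelated to it, taxon and response correlate at rb × ro in size: 0.09, 0.25 and 0.49 for 0.3/0.3, 0.5/0.5 and 0.7/0.7. If BMI correlates at 0.5 with liver fat, adjusting for BMI removes part of this. The remaining partial correlation is rb·ro(1 − 0.25)/√[(1 − 0.25rb²)(1 − 0.25ro²)], which gives 0.07, 0.20 and 0.42. On 11 df the test rejects when the sample partial correlation exceeds 2.201/√(2.201² + 11) = 0.55.

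**Per-taxon rejection rate at nominal 5%, before FDR** (simulation, 20,000 trials per cell):

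| rb/ro | Without starting fat, BMI unrelated to it | Without starting fat, BMI correlated 0.5 with it | With starting fat |
|---|---|---|---|
| 0.3/0.3 | 6.0% | 5.7% | about 5% |
| 0.5/0.5 | 12.7% | 10.1% | about 5% |
| 0.7/0.7 | 41.8% | 30.8% | about 5% |

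If rb = 0 or ro = 0, the rate is about 5% in both models.

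**After FDR control.** Further assumptions: 60 genera, 10 of them marking starting fat, Benjamini-Hochberg at 5%, BMI unrelated to liver fat. The chance of at least one flagged taxon, without versus with starting fat, is:

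- 8.0% versus 5.6% (rb 0.5, ro 0.5)
- 13.4% versus 5.2% (rb 0.5, ro 0.7)
- 31.9% versus 5.3% (rb 0.7, ro 0.7)

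**Precision.** Adjustment leaves a fraction 1 − rb² of the residual variance, so the reduction is rb²: 9%, 25% and 49% for rb = 0.3, 0.5 and 0.7. A taxon unrelated to starting fat gets the full benefit. For a related taxon the coefficient variance changes by about (1 − rb²)/(1 − ro²), which is 1 when rb = ro. There the gain is separability, not precision.

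**The case against.** **The key terms are undefined.** Response might not be a liver fat measure, and abundance might be a pre-to-post change that nothing in the article ties to starting fat. The full protocol may settle both. This stands, and it makes the point conditional. It does not remove it, because the covariate list itself is stated.

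**The repeated measures ANOVA may serve the correlation objective.** Possibly, but it does not put starting fat into the genus-level model, which has its own decision rule.

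**Starting fat may be on the causal path.** The Introduction's wording runs from microbiota to liver fat. If a taxon affects response partly through steatosis, adjustment removes part of a real association, and a taxon that forecasts response through steatosis is not strictly a false finding. This stands. The two models answer different questions, so both should be shown.

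**The article does not show that the fall depends on the starting value.** The Sample size section describes a 1.6% decrease from 2.4% in the healthy-volunteer pilot and a fall from 20.4% to 18.8% (also 1.6 points) in the group's NAFLD study. These are different populations and durations, and 1.6% is also given as the pilot's post-LGI value, so they settle little. The 20.4% comes without an SD and says nothing about spread. This stands: rb is an assumption, not an estimate.

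**BMI may carry some of the information.** It may, as the table shows. Box 1 bounds BMI from below only, just as it does liver fat, so the entry criteria give no reason to call BMI a poor stand-in or to drop it.

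A reader might infer that the model will yield false taxa, or that the 42% figure describes this trial. The documents support neither. That figure needs both correlations at 0.7, BMI unrelated to liver fat, and no FDR step.

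**Conclusion.** The point holds in a conditional form. Provided that response is a liver fat outcome and that abundance is related to starting fat, the stated model cannot separate a marker of LGI response from a marker of starting steatosis. The excess error ranges from negligible to large over correlations that the article does not supply, and it is smaller after FDR control than per taxon. This is a secondary association analysis. It is an improvement available from data already collected, not a contradiction in the plan.

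**What to change.** State that response is the post-LGI MRS liver fat fraction, and say at which visit OTU abundance is taken. Add the pre-LGI MRS liver fat fraction to the genus-level model alongside age, gender and BMI, keeping BMI. With the pre-LGI value as a covariate, using the post value or the change as outcome gives the same taxon coefficient and test, because subtracting a covariate from the outcome only shifts that covariate's own coefficient by 1.

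Report the model without pre-LGI liver fat as a sensitivity analysis, and describe taxa that appear only there as not separable from starting severity.

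The cost is one residual degree of freedom, 11 to 10. No further scan, visit or participant is needed.
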